#### Safety outcomes

We will record all AEs during the entire study period. The participants will be asked to complete a self-reported questionnaire regarding any AE every 3 weeks. The participants will also be encouraged to report AEs to the research staff via telephone when there is any AE occurrence. We will rank the severity of AEs according to the CTCAE version 5.0. The cause of the AEs will be ranked as unknown, definitely not related, probably not related, possibly related, probably related and definitely related.^29^

Moreover, we will report the mean change in the laboratory tests regarding AEs from the beginning to the end of the 12-week intervention: haemoglobin, AST, ALT, GGT, cystatin C, creatinine and eGFR.

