**Figure 1 F1:**
[figure not shown]
Flow chart of this trial. HMB, β-hydroxy-β-methylbutyrate.

**Table 1 T1:** Schedule of enrolment, interventions and assessments

Timepoint	Enrolment	Allocation	Postallocation			
	Visit 1	Visit 2	Visit 3	Visit 4	Visit 5	Visit 6
	Screening (−4 to 0 week)	Baseline (0 week)	3 weeks±2 days	6 weeks±2 days	9 weeks±2 days	12 weeks±2 days
Enrolment						
Consent	√					
Inclusion and exclusion	√					
Demographics	√					
Medical history	√					
Body height	√					
Body weight	√					
Blood pressure	√					
Heart rate	√					
BIA	√					
Allocation		√				
Interventions*						
HMB nutritional supplement+calorie restriction						
Placebo+calorie restriction						
Assessments						
Inclusion and exclusion		√				
Body weight		√		√		√
Blood pressure		√		√		√
Heart rate		√		√		√
WC		√		√		√
HC		√		√		√
IPAQ-SF		√	√	√	√	√
FFQ		√	√	√	√	√
BIA		√		√		√
Sit-to-stand test		√		√		√
HGS		√		√		√
Blood tests†		√				√
Adverse events‡			√	√	√	√
Adherence‡			√	√	√	√

*Both intervention groups will also receive dietary instruction.

†The blood tests will include glucose metabolism (fasting glucose and insulin), albumin, haemoglobin, alanine aminotransferase, aspartate aminotransferase, gamma-glutamyl transpeptidase, cystatin C, creatinine, estimated glomerular filtration rate, lipid profiles and full blood counts.

‡Weekly WeChat or telephone contacts will be performed to assess adverse events and adherence (including dietary compliance).

BIA, bioimpedance analysis; FFQ, Food Frequency Questionnaire; HC, hip circumference; HGS, hand grip strength; HMB, β-hydroxy-β-methylbutyrate; IPAQ-SF, International Physical Activity Questionnaire Short Form; WC, waist circumference.

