#### Exclusion criteria

Individuals with any of the following criteria will be excluded: (1) a history of intolerance to enteral nutrition, food (eg, lactose intolerance) or being allergic to the components of the HMB-enriched nutritional supplements (eg, soy or corn); (2) having any implants (eg, pacemakers, implantable cardioverter defibrillators and dental implants); (3) current use of other nutritional supplements or drugs that may have an impact on the effectiveness of the intervention (eg, glucocorticoids, antineoplastic drugs, antituberculosis drugs, sedatives, antipsychotics, muscle relaxants, monoamine oxidase inhibitors, antibiotics) within 3 months prior to enrolment; (4) secondary obesity caused by diseases (eg, hypothalamic diseases and hypercortisolism) or drugs (eg, glucocorticoids, insulin, tricyclic antidepressants and weight loss supplements/drugs); (5) clinically visible oedema; (6) trauma, surgery, hospitalisation, fall or fracture within 6 months prior to enrolment; (7) pregnancy, having pregnancy plans or lactation; (8) individuals who are participating in other clinical trials; (9) any acute illness (eg, acute infection, myocardial infarction, arrhythmia, myocarditis, appendicitis, etc); (10) swallowing disorders; (11) abnormal thyroid function (including hyperthyroidism and hypothyroidism); (12) history of diabetes, respiratory diseases, cardiovascular diseases, uncontrolled hypertension, kidney diseases, digestive system diseases, renal insufficiency, mental illness, neurological diseases, haematologic diseases, liver diseases (except for fatty liver), chronic infection (eg, tuberculosis), immune system diseases, joint disorders, any type of tumour; (13) alcohol consumption over two standard alcoholic beverages (20 g of alcohol/day); (14) menopause women; (15) difficulty to comply with the study protocol; and (16) other conditions that indicate the individuals are inappropriate for participation in this study.

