### Data collection, management and monitoring

Research coordinators will formally obtain the participants’ informed consent before collecting and recording data in the case report form (CRF). The assessment of outcomes will be done by assessors who are unaware of the assignment of the groups.

To ensure that participants adhere to the research strategy, all participants will be included in the WeChat group and the investigators will call them at least 1 day beforehand for each appointment and follow-up session. Participants who do not attend follow-up sessions will be asked for their reasons and telephone contacts will be made to encourage adherence to the intervention and attendance at appointments. We will also contact participants via WeChat or telephone once a week to determine if any AEs have occurred and to assess their compliance by asking each participant to complete a daily compliance record and the IPAQ-SF and FFQ questionnaires.

For the study’s quality, monitoring and auditing of the data will be carried out. Prior to the beginning of the study, there will be an introductory meeting. At every important point in the trial, such as participant enrolment, the mid-way point and the conclusion, monitoring staff will visit the institution. In addition, monitoring staff will ensure consistency in the documentation of data contained in the CRF and source document, as well as ensuring that the entire study process is conducted according to the protocol.

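### The only laboratory safety summary stated is the arm-level mean change, and no rule says whether an abnormal individual result counts as an adverse event, so an asymptomatic change in one or two participants is weakly detected

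*Protocol article*

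**What the plan says.** The abstract, the end of the Introduction and the Discussion all name safety, beside effectiveness, as something the trial will assess.

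On laboratory safety, the Safety outcomes section says: "we will report the mean change in the laboratory tests regarding AEs from the beginning to the end of the 12-week intervention". The tests listed are haemoglobin, AST, ALT, GGT, cystatin C, creatinine and eGFR. Table 1 and the Outcomes section schedule blood at baseline and at week 12 only.

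On AEs, the same section says: "We will record all AEs during the entire study period". Three routes are described:

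- a periodic form: "The participants will be asked to complete a self-reported questionnaire regarding any AE every 3 weeks" (Safety outcomes);
- spontaneous report: "The participants will also be encouraged to report AEs to the research staff via telephone when there is any AE occurrence" (Safety outcomes);
- contact started by staff: "We will also contact participants via WeChat or telephone once a week to determine if any AEs have occurred" (Data collection, management and monitoring), repeated in a footnote to Table 1.

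On grading: "We will rank the severity of AEs according to the CTCAE version 5.0". The Withdrawal criteria refer to the same scale, with an AE of grade 3 or higher as one ground. Another ground lets investigators act on signs of a complication or a new disease.

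**The concern.** Laboratory harm from a supplement usually shows first as a marked change in a few individuals, not as a small shift in everyone. An arm mean spreads such a change over all participants in the arm. A participant cannot report a raised ALT or creatinine that causes no symptoms, so none of the three AE routes would bring it to light unless the laboratory result itself is treated as a source of AEs. The article calls these tests relevant to AEs, but no sentence connects an individual value to an AE record or to a CTCAE grade.

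At stake is what the safety conclusion would mean. A report that mean ALT and mean creatinine did not differ between arms could be correct while one or two participants on one arm had large changes. A reader of the results could not tell whether that was so. The definition also decides how much is covered by the promise to record all AEs and by the CTCAE grading.

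**Working it through.** The plan gives no figure for laboratory safety, so there is none to reproduce. The check asks how far a mean can reveal a change confined to a few people.

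**Inputs from the article.** 72 participants allocated 1:1 give 36 per arm. With the 25% attrition in Sample size estimation, 36 × 0.75 = 27 per arm. The significance level is two-sided 0.05 (Statistical analysis plan section).

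**Assumptions.** The article gives no laboratory standard deviations, so the individual rise R is expressed in standard deviations (SD) of change and varied over 3, 5 and 10. The number affected in one arm, k, is varied over 1, 2 and 3. For haemoglobin and eGFR the harmful direction is a fall; the arithmetic is the same.

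**Formulas.**
- Shift of the arm mean = kR/n.
- Variance in the affected arm = 1 + (k/n)(1 − k/n)R².
- Standard error of the difference = √[(variance in affected arm + 1)/n].
- Power ≈ Φ(shift/standard error − 1.96).

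**Smallest case** (n = 36, k = 1, R = 3): shift = 3/36 = 0.083 SD; variance = 1 + (1/36)(35/36)(9) = 1.243; standard error = √(2.243/36) = 0.250; power = Φ(0.334 − 1.96) = 5%.

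**Largest case** (n = 27, k = 3, R = 10): shift = 30/27 = 1.11 SD; variance = 1 + (3/27)(24/27)(100) = 10.877; standard error = √(11.877/27) = 0.663; power = Φ(1.675 − 1.96) = 39%.

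| n per arm | k | R = 3 | R = 5 | R = 10 |
|---|---|---|---|---|
| 27 | 1 | 6% | 8% | 13% |
| 27 | 2 | 11% | 17% | 25% |
| 27 | 3 | 17% | 28% | 39% |
| 36 | 1 | 5% | 7% | 12% |
| 36 | 2 | 9% | 15% | 24% |
| 36 | 3 | 15% | 24% | 36% |

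These figures are on the generous side. The formula is a normal approximation that lets the number affected vary around k. Simulating the t-test with exactly k affected participants (20,000 trials per cell) gives about 2% to 20% over the same grid, because the outlying values inflate the variance that the test uses.

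**Comparison with a general shift.** For 80% power, every participant in the arm would have to move by 0.67 SD (n = 36) or 0.78 SD (n = 27).

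**What a count would add.** If the true rate of such changes were 5% (an assumption), the chance of at least one affected participant in the arm is 1 − 0.95^27 = 75% or 1 − 0.95^36 = 84%. A count by grade would show each affected participant who has a week-12 sample.

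**The case against.** The strongest reply is that this is a condensed article. Shift tables, listings and rules for turning a laboratory value into an AE are often placed in the full protocol or the SAP, and neither is shown. That stands for table layout, which is not criticised here. It does not fully answer the point, because the article does choose a laboratory safety measure, and the one it chooses suits the question poorly. Whether a laboratory abnormality is an AE is a definition and not a matter of layout.

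A second reply is that the mean change is promised as a description and not as a test, so power is only a yardstick. This is fair. A large enough change would also show in a description. As an illustration, assume ALT changes with mean −8 and SD 15 U/L (neither is from the article) and 27 participants per arm. One participant at +150 brings the arm mean to (26 × −8 + 150)/27 = −2.1. Two bring it to (25 × −8 + 300)/27 = +3.7, and the arm mean is then positive in roughly 90% of simulated trials. The SD in that arm would be about 34 with one such participant and 45 with two, against 15 in the other arm, so a reported SD would be a clue. The Safety outcomes section does not mention an SD, however, and neither statistic says how many participants were affected or how severely.

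Three stronger readings are tempting, and the document does not support them:

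- A reader might infer that such a change would go unseen. The article does not say that individual results go unreviewed. Each sample goes to the hospital laboratory, all AEs are to be recorded without limit to those reported by participants, and investigators may act on signs of a complication.
- A reader might infer that AEs are found by self-report alone. Staff also ask every week. That is active enquiry, although it still relies on the participant's answer.
- A reader might infer that weight loss will lower liver enzymes in both arms and mask rises, since fatty liver is not an exclusion. The article gives no data for this, and the dilution argument does not need it.

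**Conclusion.** The point holds as a weakness in the stated safety measure, together with an undefined link between laboratory results and AEs. For a change confined to 1 to 3 participants in one arm, comparing arm means has about 5% to 39% power. This rests on an assumed individual change of 3 to 10 SDs and on 27 to 36 participants per arm; the article supplies the arm sizes but not the laboratory variability. It remains possible that an investigator or a fuller document would pick up individual abnormalities, so the article cannot be said to rule that out. The primary outcome, the sample size and the data collected are unaffected. The change is worth making because safety is a named aim and the remedy uses data and a grading scale already in the plan.

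**What to change.** In Safety outcomes, keep the mean change and add two sentences to this effect:

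1. For each listed laboratory test, the number and percentage of participants in each arm whose CTCAE v5.0 grade worsens from baseline to week 12 will be reported. Where CTCAE has no grade for a test, position against the laboratory's reference range will be used.
2. Such worsening will be recorded as an AE whether or not the participant reports it.

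Because the Withdrawal criteria refer to AE grade, the sponsor should check that the two sections still read consistently once laboratory findings are defined as AEs. How they are reconciled is a clinical matter for the sponsor.

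Cost: one extra table from samples already planned, with no new visits, tests or participants. AE counts may look slightly less favourable than under participant report alone.

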#### Feasibility outcomes

We will record the recruitment rate and completion rate to assess the feasibility of this trial. Additionally, the adherence rate to the interventions will be calculated. Moreover, we will record the reasons for participants’ ineligibility and for dropping out of this trial.

### Data collection, management and monitoring

Research coordinators will formally obtain the participants’ informed consent before collecting and recording data in the case report form (CRF). The assessment of outcomes will be done by assessors who are unaware of the assignment of the groups.

To ensure that participants adhere to the research strategy, all participants will be included in the WeChat group and the investigators will call them at least 1 day beforehand for each appointment and follow-up session. Participants who do not attend follow-up sessions will be asked for their reasons and telephone contacts will be made to encourage adherence to the intervention and attendance at appointments. We will also contact participants via WeChat or telephone once a week to determine if any AEs have occurred and to assess their compliance by asking each participant to complete a daily compliance record and the IPAQ-SF and FFQ questionnaires.

For the study’s quality, monitoring and auditing of the data will be carried out. Prior to the beginning of the study, there will be an introductory meeting. At every important point in the trial, such as participant enrolment, the mid-way point and the conclusion, monitoring staff will visit the institution. In addition, monitoring staff will ensure consistency in the documentation of data contained in the CRF and source document, as well as ensuring that the entire study process is conducted according to the protocol.

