### Blinding

By using identical doses and appearance of HMB-enriched nutritional supplements and placebos, participants and outcome assessors will be blinded to group allocation.

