### Interventions

The participants will be randomly assigned into two groups: the intervention group and the control group. The two groups will be randomly labelled A or B. The participants in both groups will perform a calorie restriction diet. They will receive individualised nutritional guidance from professional dietitians by video regarding calorie restriction strategies. The principle for calorie restriction will be based on the equation: energy intake=ideal BW (ie, height (cm)−105)×25 kcal/kg/day.^23^ The compliance will be followed via a WeChat group and telephone. The intervention duration in both groups will be 12 weeks.

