#### Intervention group

The participants in the intervention group will receive oral HMB-enriched nutritional supplements (65 g, once daily) in powder form packaging in opaque plastic bottles, which include soybean isolate, protein, whey protein, casein, HMB, L-glutamine, wheat oligopeptide, medium-chain fatty acids, vitamin D, vitamin E, konjac powder and fish oil powder.

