#### Control group

The participants in the control group will receive a placebo (maltodextrin 65 g once daily) in powder form packaging in the same opaque plastic bottles as the intervention.

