## Discussion

This study will be a randomised, double-blind, parallel-group, placebo-controlled trial aiming to explore the effectiveness and safety of HMB-enriched nutritional supplements for improving muscle mass and muscle strength in obese adults during the weight loss process using calorie restriction. It will determine the feasibility of future large-scale clinical trials on HMB-based interventions for improving body composition (especially muscle health) in obese adults when performing weight loss plans.

The effectiveness of HMB for improving muscle mass and muscle strength has been well studied in athletes, healthy adults, older adults and patients with cancer.^33^ However, we found only two clinical trials addressing the effectiveness of HMB on muscle health in obese adults.^34 35^ In 2019, an RCT conducted in Iran demonstrated that supplementing with HMB for 6 weeks reduced weight, waist and abdominal circumference, and even increased strength without resistance training, and without affecting lean mass, in sedentary and overweight women.^34^ Most recently, Rondanelli *et al*^35^ conducted an RCT in obese or overweight Italian menopausal women. Using an oral nutrition supplement containing arginine, glutamine and HMB for 4 weeks, they observed that visceral adipose tissue and BFM were statistically significantly reduced, whereas fat-free mass (mainly muscle mass) remained the same.

Our trial has some strengths. First, it will be the first to evaluate the effectiveness of HMB-enriched nutritional supplements for improving muscle health in Chinese obese adults. Second, we will use a double-blinded design to minimise bias due to demand characteristics, the placebo effect and measurement bias. Last, we will focus on muscle mass and fat mass and muscle function (ie, HGS and physical performance).

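### One WeChat group shared by both arms and used to follow compliance puts participant blinding at avoidable risk

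*Protocol article*

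**What the plan says.** Under Data collection, management and monitoring, the protocol article says that "all participants will be included in the WeChat group". Under Interventions it adds: "The compliance will be followed via a WeChat group and telephone". Both sentences speak of a single group, and neither separates the arms.

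The Blinding section gives its basis in one sentence: "By using identical doses and appearance of HMB-enriched nutritional supplements and placebos, participants and outcome assessors will be blinded to group allocation". The two product sections add that both are powders of 65 g once daily in the same opaque bottles. The active powder contains "soybean isolate, protein, whey protein, casein, HMB, L-glutamine, wheat oligopeptide, medium-chain fatty acids, vitamin D, vitamin E, konjac powder and fish oil powder". The control is a "placebo (maltodextrin 65 g once daily) in powder form packaging in the same opaque plastic bottles as the intervention".

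The article also plans contact outside the group: "We will also contact participants via WeChat or telephone once a week to determine if any AEs have occurred and to assess their compliance". The footnote to Table 1 repeats this weekly contact. The Discussion counts blinding among the trial's strengths: "we will use a double-blinded design to minimise bias due to demand characteristics, the placebo effect and measurement bias".

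**The concern.** A participant who takes one powder alone for 12 weeks has nothing to compare it with. A group that holds both arms supplies the comparison. Because compliance with the assigned powder is among the things followed there, the product is a natural topic. The stated matching covers what the product looks like and how it is packed. Nothing in the article says that taste, smell or mixing behaviour match, and the ingredient lists give reason to expect differences.

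If participants infer their arm, three kinds of result are exposed:

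- Grip strength and the sit-to-stand test, which depend on effort.
- IPAQ-SF, FFQ and adverse events, which are self-reported.
- Adherence and dropout. The Statistical analysis plan section removes from the analysis anyone who received less than 75% of the planned intervention or who lacks the primary outcome. Adherence that differs by perceived arm would therefore change who is compared, even in what is called the full analysis set.

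**Working it through.** No formula tests the main point, so the first step is to set the statements side by side.

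1. **Membership.** All participants are in the group (Data collection, management and monitoring), so both arms are.
2. **Use.** Compliance is followed through a group and by telephone (Interventions). The group is more than a list for appointment reminders.
3. **Matching stated.** Dose and appearance (Blinding); powder form, once-daily use and opaque bottle (Intervention group, Control group).
4. **Contents.** Several proteins, HMB, konjac and fish oil, among others, against maltodextrin.
5. **Protection claimed.** Double-blinding is offered against demand characteristics, the placebo effect and measurement bias (Discussion).

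Items 1 and 2 create a channel between the arms. Items 3 and 4 leave a difference that the channel could reveal. Item 5 shows what depends on its not being revealed.

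The second step asks which parts of the blinding the channel reaches.

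| Element | Reached by the group? |
|---|---|
| Participants | Yes, directly |
| Outcome assessors (Blinding; Outcomes) | Only if information is passed on |
| Statistician (Statistical analysis plan) | Only if information is passed on |
| Bioimpedance reading (Primary outcome) | Not the reading itself; muscle mass can still change through diet and activity |
| Investigators, blinded according to the Abstract | Possibly, if they read the group |

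The third step illustrates sensitivity. The plan states no figure for this, so there is none to reproduce. Suppose that there is no true effect and that knowledge of the arm shifts the mean difference by d standard deviations. The chance that a two-sided 5% two-sample t-test is significant is then

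P(|T| > t_crit), where T is noncentral t with 2n − 2 degrees of freedom and noncentrality d × √(n/2).

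Inputs: 72 randomised 1:1 gives 36 per arm. The 25% attrition rate in Sample size estimation gives 36 × 0.75 = 27 per arm. The shifts d = 0.1, 0.2 and 0.3 are assumptions and appear nowhere in the documents.

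| d (assumed) | Noncentrality, n = 27 | Error rate, n = 27 | Noncentrality, n = 36 | Error rate, n = 36 |
|---|---|---|---|---|
| 0.1 | 0.37 | 6.5% | 0.42 | 7.0% |
| 0.2 | 0.73 | 11.1% | 0.85 | 13.3% |
| 0.3 | 1.10 | 19.1% | 1.27 | 24.1% |

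These rates show how little shift it takes to matter. They do not estimate the bias that this group would cause.

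**The case against.** The strongest reply is that the article nowhere says members may post freely, discuss the powder or report compliance in front of each other. Much of the detailed checking reads as individual: each participant fills in a daily compliance record, adverse events go into a questionnaire or to staff by telephone, and weekly contact is by WeChat or telephone. Rules for the group and matching of flavour could well sit in the full protocol, which is not shown. This stands as a limit on certainty. It does not remove the point, because the shared group and its use for compliance are stated features of the plan and not omissions.

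A reader might infer that a single post would unblind the whole trial. The documents do not support that. They show an opportunity for participants, not an event and not its reach, and assessors and statistician are blinded separately.

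A reader might also infer contamination from diet or exercise advice passing between arms. That does not follow either. Both arms receive the same calorie restriction with individualised dietitian guidance, so such advice moves no randomised component across.

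Two further objections hold in part. Some participants might guess their arm without any group, so the illustrative error rates cannot be attributed to the group alone, and removing the group would not cure a sensory mismatch. And with 25% attrition allowed for, peer support may help retention, which is a genuine benefit to weigh.

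**Conclusion.** The point holds as a risk to participant blinding that the plan creates and can cheaply avoid. It rests on the plain reading that there is one group for both arms, and on the assumption that members can see each other's messages. It also assumes that powders so different in content can be told apart by taste, smell or mixing once compared; the article neither claims nor denies sensory matching.

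The outcomes most exposed are the effort-dependent tests and the self-reported measures, followed by the make-up of the analysed set under the 75% rule. The primary outcome is exposed only indirectly, through behaviour and through who is analysed. The size of any bias cannot be derived from the documents. The change is worth making before enrolment, since participant blinding once lost cannot be restored.

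**What to change.** Amend the Interventions and the Data collection, management and monitoring sections as follows:

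- Follow compliance one-to-one, through the weekly WeChat or telephone contact already planned, and drop the shared group for this purpose.
- If a group is kept for reminders, make it announcement-only, so that members cannot post.
- Instruct participants not to discuss the product with each other.

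The cost is slightly more messaging work for staff and some loss of peer support. Sample size, visit schedule and analysis are unchanged.
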